
### Monitoring

The responsible research team members meet once a week to monitor the process of the study, the data collection, and identification of need for adjustment. Additionally, the conducted EMDR interventions will be supervised during the respective execution. No interim analysis will be performed. There are no stopping guidelines for premature termination of the study.

### Concomitant care, serious adverse events

Due to ethical considerations, participants can receive psychotherapeutic treatment or psychopharmacological medication during the study. The existence of simultaneous psychotherapy or psychopharmacological medication will be surveyed in every data collection point so that any changes in this regard are recorded. By conducting the study, no serious adverse events (SAE) are expected. Cases will be supervised regularly by an external EMDR supervisor. However, if in any case of a serious adverse event happens, this will be immediately and directly reported contact to the study team and the principal investigator. Serious adverse events include suicidal ideation, severe self-harm, or severe and ongoing exacerbation of the symptoms of secondary traumatization in the context of EMDR treatment. These will be reported systematically in non-standardized language as well as discontinuation of the study participations for other reasons. Responsible therapists will be informed about this procedure prior to the study. It will be reported by Serious Adverse Event Report Form [54]. Handling of adverse events will be decided individually. Therapeutic treatment through the outpatient clinic of the department is possible if required. A short-term increase in psychological stress is inherent in the EMDR procedure, as it is a trauma confrontation procedure. This normally subsides within a few days. This is not systematically reported as harm, as it could arise as part of the treatment, but will be discussed in the joint sessions with the responsible therapist.

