### Primary outcome measure

The questionnaire-based data collection will be carried out upon the initial screening appointment (T1) for each group. For the intervention group, the second data collection point (T2) is around 6 weeks after T1, after the last session for the intervention, then 4 weeks (T3) and 8 weeks (T4) after T2. For the waitlist control group, T2 will be 6 weeks after T1, then after their last session (T3) and 4 weeks (T4) after T3. Also see Fig. 1. The participants will receive the link to the online questionnaires as well as reminders, if necessary, by email.

Secondary traumatic stress will be surveyed with the Questionnaire for Secondary Traumatization (“Fragebogen zur Sekundären Traumatisierung,” FST) [31]. This questionnaire surveys different symptoms of secondary traumatic stress based on diagnostic criteria of DSM-V for posttraumatic stress disorder, such as rumination, intrusions or nightmares, avoidance behavior, and, furthermore, cognitive or behavioral changes. The frequency of the above symptoms in the last week is assessed by 31 items on a 5-point Likert scale (1 = never, 5 = very often). From a sum score of ≥ 65, moderate secondary traumatic stress can be assumed. The structure of the questionnaire is similar to the Impact of Event Scale [40] and is designed to be used in professional context. It showed good internal consistency for the total score (Cronbach’s *α* = 0.94) in three different samples of professionals.

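### Severe symptom exacerbation is a serious adverse event only under EMDR, so its counts cannot be compared with the waiting period

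*Protocol article*

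**What the plan says.** All of the event wording is in the protocol article, Concomitant care, serious adverse events.

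- **Definition.** The list opens with suicidal ideation and severe self-harm and ends with "severe and ongoing exacerbation of the symptoms of secondary traumatization in the context of EMDR treatment".
- **Reporting.** If such an event happens, "this will be immediately and directly reported contact to the study team and the principal investigator". That sentence names no reporter. The one group said to be briefed is the therapists: "Responsible therapists will be informed about this procedure prior to the study".
- **Other items reported.** Events are reported "as well as discontinuation of the study participations for other reasons", with no limit to one group.
- **Expected distress.** A brief rise in stress after a session is treated as part of the method: "This is not systematically reported as harm".
- **Asked at each assessment.** "The existence of simultaneous psychotherapy or psychopharmacological medication will be surveyed in every data collection point". The section mentions no event question alongside it.

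On timing, Primary outcome measure states: "The questionnaire-based data collection will be carried out upon the initial screening appointment (T1) for each group". T2 follows about six weeks later in both groups. For the intervention group it comes after the last session, and for the waitlist group it comes before any EMDR. Statistical analyses names the control group's T1 to T2 wait as a period of interest for the FST. It restricts the analysis to participants with pre and post questionnaires and, in the intervention group, at least two sessions.

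**The concern.** An adverse event definition that contains exposure to the treatment cannot be met by anyone not yet exposed. Here the qualifier sits inside the definition, where a separate judgement of relatedness would normally be made after the event is recorded. For this category, the waitlist count over T1 to T2 is zero whatever happens to those participants.

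This category matters more than its place at the end of the list suggests. The passing rise in distress is set aside as expected, so severe and lasting worsening is the main treatment-specific harm signal that the event record keeps. Interpreters who already score at or above the FST cut-off may also worsen while waiting, particularly if they go on working. Some worsening in the EMDR group would therefore be expected without any effect of EMDR, and the waitlist group is the only source for that background rate. If the final report lists exacerbations in the EMDR group beside a zero for the wait, that zero would come from the definition and would tell the reader nothing.

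**Working it through.** The protocol article gives no harm rate or event figure to reproduce, so the check sets its statements side by side for the T1 to T2 period.

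| Item | EMDR group | Waitlist group | Source section |
|---|---|---|---|
| Treatment status | In EMDR, sessions about weekly | No EMDR yet | Primary outcome measure; Intervention |
| Severe exacerbation as an SAE | Can be met | Cannot be met | Concomitant care, serious adverse events |
| Suicidal ideation, severe self-harm | Can be met | Can be met, if the EMDR qualifier attaches only to the last item | Same |
| Discontinuation | Reported | Reported | Same |
| Contact with the persons briefed on reporting | At screening and in sessions | At screening; no session described during the wait | Same; Randomization; Intervention |
| FST at T1 and T2 | Yes | Yes | Primary outcome measure |

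**Step 1: the definition.** The second row differs between groups because of the wording alone. This is a stated rule.

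**Step 2: who reports.** Therapist reporting is implied by the briefing sentence but not stated. The implied route has more opportunities in the EMDR group. This is a weaker point than Step 1 and only adds to it.

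**Step 3: how far the FST fills the gap.** It measures the symptoms concerned, in both groups, at both times. Three limits remain:

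- It asks about the last week, so worsening that eased before T2 is not captured.
- The planned model compares growth rates between periods. No count of individual deterioration, reported as harm, is planned.
- The per-protocol set excludes a participant who worsens and returns no post questionnaire, and an intervention participant who stops after the first session.

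**Step 4: what a comparison could show once the wording is corrected.** Inputs are the target of 40 (Statistical analyses) and alternating allocation (Randomization), giving 40 / 2 = 20 per group. With all events in one group, the two-sided Fisher p-value is 2 × C(20,k) / C(40,k):

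- k = 4: 2 × 4,845 / 91,390 = 0.106
- k = 5: 2 × 15,504 / 658,008 = 0.047

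Only a split as extreme as 5 against 0 would fall below 0.05. The correction makes the counts comparable but does not give the trial power for harm.

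**The case against.** The strongest reply is that worsening during the wait is measured. The FST is collected in both groups at T1 and T2, the waiting period is a named period of interest, and the category concerns ongoing exacerbation, which is the kind most likely still to show at T2. This stands. A reader might infer that deterioration while waiting goes unrecorded, but the document does not support that.

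A reader might also infer that harm is ascertained in one group only. That too goes beyond the text. The list of events is open, suicidal ideation and self-harm are not clearly tied to EMDR, and discontinuations are reported without restriction. Nor are waitlist participants out of sight: they see a therapist at screening, the team meets weekly to monitor the study, and data collection is checked with reminders at regular intervals. None of this is described as an event-reporting route, but it rules out saying that there is no contact.

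Third, who reports during the wait and what the report form asks are details that an article commonly leaves to the full protocol. Their absence is not a finding here. The point rests on the definition, which the article does state.

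Finally, it is tempting to size the defect by the upper limit for no events in 20 treated, 1 − 0.05^(1/20) = 13.9% (one-sided 95%), or by counting therapist contacts. The limit follows from the group size and would be the same after the correction. At three to six sessions, contacts would be 60 to 120 for 20 participants, which describes opportunity to notice events and not missed events. Neither figure measures the defect.

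**Conclusion.** The point holds in a limited form. Counts of severe and ongoing exacerbation recorded as serious adverse events are not comparable between EMDR and waiting over T1 to T2, because the definition excludes waiting participants. The FST at T1 and T2 partly makes up for this, but no individual tabulation as harm is planned and the analysis set would leave out some of the participants of most interest.

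The extent is one event category, for about six weeks, in about 20 of the 40 planned participants. It ends when the waitlist group starts EMDR, and the primary efficacy analysis is unaffected. How many events would be missed cannot be estimated from the document.

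The conclusion assumes that the definition is applied as written and that no waitlist participant receives study EMDR before T2. It does not depend on whether the qualifier also covers the first two events in the list. If it does, the problem extends to them. The change is worth making because it is cheap, and should be made before the event data are compiled.

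**What to change.** 1. Delete the qualifier that ties exacerbation to EMDR from the event definition. Count events from T1 in both groups, and record relation to EMDR as a separate item on the event form.
2. Put the same event question to both groups in the T2 online survey, next to the existing question on concomitant treatment.
3. Tabulate individual FST worsening from T1 to T2 by allocated group, for everyone with data and not only the per-protocol set. Fix the threshold for worsening in advance, and show the number with missing T2 scores in each group.
4. Present these results descriptively, without a claim that excess harm is shown or excluded.

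The cost is a wording change, one survey item, one table and probably a few more event forms. If participants have already passed T2, the event question cannot be asked of them at that point, and the report should say so; the FST table can still be made from data already collected. The change concerns recording and reporting only and alters no clinical management.

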### Intervention

Participants will be allocated to a therapist, medical doctor or psychologist of the department who will have completed, at least, EMDR training level 1. The EMDR treatment that will be carried out is comprised of 8 phases according to Shapiro [51]. In the first session, phases 1 and 2 will be conducted. The first phase includes the establishment of a therapeutic relationship as well as the exploration of the symptomatology and the trauma history. In this case, the therapist will comprehensively examine the symptoms of secondary traumatization including distressing situations relating to their work in refugee care in the present. Emotion regulation strategies of the participant will be elaborated. With help of the “adaptive information processing” model (AIP), the therapist and the participant will work out underlying stress situations from the professional context. According to the AIP model, traumatic memories, but also other “live events” or disturbing experiences that do not accord to the trauma criteria, can create a “pathogenetic memory.” These pathogenetic memories are stored in a dysfunctional way, are not connected to adaptive memory networks, and, subsequently, cause symptoms. Based on this assumption, repeated exposure to details of refugees’ traumatic experiences leads to dysfunctional storage of this experience of the affected interpreters [52, 53]. The therapist and the participant will carve out the respective distressing situations and classify them on a scale from 0 to 10 (subjective level of disturbance, SUD), as stated in the EMDR manual. Additionally, the participant will be introduced to the EMDR technique itself. An imaginative exercise, “safe place,” will be executed together and reinforced with EMDR technique. Techniques to stop flashbacks will be discussed. Additionally, the participant will receive a further imagination exercise, called “safe exercise,” that helps distancing oneself from disturbing thoughts. The first session takes 50–60 min. Phase 3–7 will be conducted in the following sessions according to the EMDR standard protocol. Phase 8 will be performed at the beginning of every exposition session. The EMDR standard protocol will be applied. This means that the disturbing memories will be worked on in a specific (“the first, the worst, the last”). However, by mutual agreement, the order in which the stressful memories are processed is left open to the therapist and the participant, if this leads to greater openness to therapy and adherence. Sessions will take place once a week; the therapist and participant will agree mutually on the date of the sessions, and they can be adapted to the participants’ needs. The confrontational sessions ends ideally when the SUD is 0. However, depending of the processed content, this cannot always be achieved, for example if the participant processes earlier stressful memories through so-called affect bridges. In this case, the session can be closed if SUD is not 0 but only reduced from the initial level. In this case, work on this memory will continue in the following session (phase 8). The processing time can differ between patients and takes around 60–90 min. A maximum of six sessions will be conducted. The number of sessions will be adapted to the participants needs. This implies that within the span of these six sessions, the stressful situations related to the participant’s work with refugees, which the participant seeks to address, are systematically managed. If a complete reduction of the SUD is not achieved within a single session, the issue may be resolved over 2–3 sessions. However, it is generally expected that each session is self-contained, as the nature of the underlying stressors suggests that a full reduction in SUD can be accomplished within one session. Consequently, the number of sessions corresponds to the number of specific situations requiring attention. Conducting fewer than six sessions does not imply that any therapeutic content is omitted. Participants in both groups receive the same intervention.

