### Statistical analyses

The quantitative data will be monitored and analyzed by the study team and colleagues of the research group using SPSS [55]. As the statistical evaluations are carried out by the study team with the support of the biostatistician, blinding is not performed. Baseline characteristics will be compared to assessed differences of the intervention and control group, especially regarding the symptom load of secondary traumatization symptoms as well as on the presence of self-experienced traumatic events and PTSD symptoms. The effectiveness of the EMDR intervention will be assessed using a piece wise growth curve model [56], a type of the latent growth curve model, based on the assumption that change of symptomatology along the study duration is not linear but depends to certain change points. In this model, growth rates between different time periods are compared. The main criterion of interest is the symptom load of secondary traumatic stress assessed with the FST. Further parameters to be analyzed are symptom load of depression, anxiety, and somatic distress as well as professional quality of life and quality of life. For the data collected, time periods of interest are before and after the intervention for intervention group (T1–T2) and waitlist control group (T2–T3), after the intervention to follow up for both groups (intervention group T2–T3/T4, control group T3–T4), and before and after the waiting period for the control group (T1–T2). Covariates will include current psychiatric treatment, current psychopharmacological prescription or medication change, and personal traumatic experience. The data of all randomized participants who filled out the pre-and post-questionnaires and, from the intervention group, who completed at least two sessions (one preparatory session with investigation of the experiences that will be processed (phases 1–2) and at least one confrontational session (phase 3–7/8) will be included in the analysis (per-protocol analysis). Reasons for incomplete participation in the intervention will be presented descriptively. With regard to the calculation of the sample size for a piece wise growth model, there is only scarce literature on how to do so [57]. Therefore, the sample size is calculated on the basis of analysis of variance (ANOVA) with repeated measures. According to literature, EMDR shows large effect sizes (*g* = 1.01 (CI 95% 0.42 to 1.62). For the present study, however, the effect size of EMDR on secondary traumatization is not known yet. Therefore, a conservative calculation with a medium effect (*d* = 0.5) was carried out. Assuming a type I error of *α *= 0.05 and a statistical power of 0.8, a sample size of *n *= 34 is calculated [58]. Assuming a drop-out rate of 18% [59], a sample size of 40 is aimed for. Missing data will be first identified and analyzed. No further measures will be carried out in case of missing data < 5%. If > 5% of the data are missing, it will be examined whether these are related to certain variables, such for example with symptom burden and whether patterns can be recognized. If these data are missing at random, no further procedures will be carried out. If missing values are systematically related to one of the recorded variables, a multiple imputation can be performed [60]. Due to a lack existing studies, the distribution of the data cannot be estimated. Therefore, the collected data is first checked for normal distribution and if not normally distributed transformed in order to carry out the analyses with transformed data.

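### Short-term distress after EMDR sessions is excluded from systematic harm reporting because treatment may cause it, so no planned result could support the statement that it subsides within days

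*Protocol article*

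**What the plan says.** The rule is in the protocol article under Concomitant care, serious adverse events. It has three parts.

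- The reaction is expected: "A short-term increase in psychological stress is inherent in the EMDR procedure, as it is a trauma confrontation procedure". Its course is asserted: "This normally subsides within a few days".
- It is exempted, with a reason: "This is not systematically reported as harm, as it could arise as part of the treatment".
- What takes the place of reporting is a conversation: "but will be discussed in the joint sessions with the responsible therapist".

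The same section names as SAEs suicidal ideation, severe self-harm, and worsening of secondary traumatization symptoms that is both severe and persistent. These go to the study team and principal investigator at once and on a form. Discontinuations for other reasons are also reported. Statistical analyses adds a descriptive account of why participants did not complete the intervention.

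**The concern.** The reason given points the wrong way. A reaction that treatment is expected to provoke is what a harms table of expected, non-serious events is for. Being expected justifies separating it from SAEs, but not leaving it out of the report.

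This is a stated rule and not a detail left to a fuller document. A later analysis plan could report the reaction systematically only by reversing what the article says.

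At stake is tolerability. The Abstract says the study will assess whether EMDR could be acceptable as well as effective, and the Background describes knowledge of effective treatment for this burden as scarce. A reader deciding whether to offer confrontation sessions to working interpreters will want to know how many had a difficult few days afterwards, how difficult, and for how long. As planned, the report could repeat the protocol's assurance but could not support it with data.

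**Working it through.** The article states no figure to reproduce, and the point does not depend on alpha, power, effect size or sample size. The check is whether any other planned measurement would report the same event.

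1. **Questionnaires (Primary outcome measure).** The intervention group is assessed at T1 and next at T2, after its last session. The waitlist group is assessed at T1, at T2 after six weeks of waiting, and at T3 after its last session. In both groups, no planned questionnaire falls between the first and the last session.
2. **Recall windows.** The FST (the secondary traumatization questionnaire) asks about the past week, and the WHO-5 about the past two weeks (Quality of life). The delay between the last session and the next questionnaire is not fixed. Since "Sessions will take place once a week", a one-week window reaches back to about the latest session at most, and a two-week window to about the last two. In either case one score mixes a post-session reaction with general symptom load and links nothing to a session.
3. **Subjective disturbance ratings (Intervention).** The 0 to 10 rating concerns the memory being processed and guides when a session may close. It is not named as an outcome or harm measure, and it does not describe the days after a session.
4. **SAEs.** Worsening must be both severe and persistent. Severe but brief distress does not qualify, nor does moderate distress that lasts.
5. **Discontinuations and reasons for incomplete participation.** These describe people who stop, not people who continue while distressed.
6. **Team meetings and supervision (Monitoring; Concomitant care).** Neither is described as recording this reaction.
7. **Discussion with the therapist.** It is planned as part of care. No count or summary is derived from it.

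None of the seven yields a planned count, severity or duration.

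**Can the reaction be captured within the existing schedule?** Largely yes. "Phase 8 will be performed at the beginning of every exposition session", and the stated course of a few days is shorter than the planned weekly interval, so a question at the next session would normally come after the reaction should have passed. The limit is the last session, which has no later one. With "A maximum of six sessions will be conducted" and the first preparatory, a participant has at most 6 − 1 = 5 confrontation sessions, of which at most 5 − 1 = 4 are followed by another session. The analysis set requires only "at least one confrontational session", and a participant at that minimum has 1 − 1 = 0. The last session therefore needs a separate question.

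**The case against.** The strongest reply is that little is left uncovered. The serious end is reported immediately, discontinuations and reasons for incomplete participation are described, an external supervisor follows the cases, and the reaction is disclosed openly and discussed with the therapist. The article's own Discussion explains the practical aim as whether the offer meets participants' needs and is used, and it never uses the word tolerability. The remark about a few days is background to the rule, not a planned result. All of this is fair, and it keeps the point small. It does not supply a reason for leaving an expected reaction out of the report.

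Three stronger readings are tempting, and the article does not support them.

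- A reader might infer that the trial will have no information on how often the distress occurs. The article does not say whether therapists write down these discussions. It shows only that no systematic reporting is planned.
- A reader might take the number of confrontation sessions as the size of the problem. It shows how many occasions there are for a note. It does not show how often distress occurs or how much it matters, and the article gives no frequency.
- A reader might conclude that serious harm goes unreported or that the effect estimate is biased. Neither follows.

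It also stands that counts collected during treatment would be uncontrolled, because waiting participants have no matching rating. Attribution would be imperfect too, since participants may keep interpreting and may receive other psychotherapy or medication. That limits interpretation but does not argue against describing the reaction.

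**Conclusion.** The concern holds in a limited form. The article exempts an expected treatment reaction from systematic harm reporting for a reason that does not support the exemption, and no other section plans to count or summarise it. The planned harms report would consist of SAEs and discontinuations, and the statement that the distress normally clears within days could not be supported from planned data. The primary outcome, the effect estimate and SAE reporting are unaffected.

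The number of participants concerned cannot be estimated from the article. The conclusion rests on reading the article as the current plan, and on no other document reversing the stated rule. It is worth correcting because the correction is cheap, not because the trial's main result is at risk.

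**What to change.** Replace the exemption with: *Expected transient distress is recorded and reported separately from SAEs, as an expected non-serious event during treatment.*

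- **During treatment.** At the start of each session that follows a confrontation session, the therapist notes whether distress rose after the previous one, how severe it was, roughly how many days it lasted, and whether it is still present.
- **Last session.** Ask the same at an existing post-treatment questionnaire, preferably one completed at least a week later, or state that the last session is not covered.
- **Report.** One descriptive table by participant and by session, labelled as uncontrolled counts.
- **SAEs.** Leave immediate reporting as it is. An escalation rule based on distress persisting over consecutive sessions should not be added here: participants with few sessions could not meet it, and it would sit badly with immediate reporting.

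**If treatment is already complete.** Trial status expected recruitment to end about June 2024. On that schedule the last waitlist participants would finish about 6 weeks of waiting + up to 6 weekly sessions = 12 weeks later, before any shift in session dates. The remedy is then a sentence in the report: transient distress was not systematically quantified, and its resolution within days is not presented as a finding.

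**Cost.** One sentence of protocol text, a brief note at no more than 40 × 4 = 160 sessions if all 40 planned participants receive the maximum, one question and one table. No new visit or staff is needed. The downsides are the extra documentation, possible under-reporting to the treating therapist, longer recall for the last session, and possibly an ethics amendment.
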